### Primary outcome

#### Study phase 1

Feasibility and safety of the QI-management protocol will be assessed, including the need to discontinue the primary stabilisation approach, any protocol deviations with documented reason, and the number of adverse events in the delivery room. Safety assessments are based on any unintended events directly related to the bedside stabilisation and neonatal parameters, including:•Temperature at ICU admission•Peak haemoglobin level and the presence of polycythaemia (venous haematocrit >0.65 L/L) within 24 hours of age•Highest bilirubin level recorded during ICU admission and the need for phototherapy and/or exchange transfusion for hyperbilirubinaemia within 7 days after birth or before neonatal arterial switch operation)Maternal parameters include estimated blood loss.

#### Study phase 2

The primary clinical outcomes are the incidence and severity of PPHN, assessed by pre- and postductal SpO_2_ differences, echocardiographic findings (continuous right-to-left shunting across the ductus arteriosus from the pulmonary to the systemic circulation, or a predominant right-to-left shunt throughout systole), and the frequency, timing, and escalation of invasive respiratory and circulatory interventions.

### Secondary outcome

Secondary outcome measures for both study phase 1 and study phase 2 include:•Timing of umbilical cord clamping: Measured in minutes after birth.•Trends in vital parameters: Heart rate, pre- and postductal SpO_2_ and blood pressure measurements will be averaged per minute and analysed for the first 72 hours after birth.•Respiratory and circulatory interventions: Frequency and types of respiratory and circulatory interventions after birth, including noninvasive and invasive respiratory interventions, administration of iNO administration, balloon atrial septostomy, and extracorporeal membrane oxygenation.•Survival proportion: Preoperative survival (ie, before arterial switch operation).•**Pressure differences across the ductus arteriosus**: Ductus arteriosus pressure gradient, estimated from Doppler-derived velocities measured by echocardiography during the cardiac cycle over the first 72 hours after birth, with measurements obtained at admission and at least once every 24 hours.

### Additional neonatal outcomes for study phase 2:

•Neonatal parameters as described in phase 1, including infant temperature at ICU admission, highest infant haemoglobin level, and presence of polycythaemia; highest bilirubin level/need for phototherapy or exchange transfusion•Apgar scores at 1, 5, and 10 minutes after birth•Possibility, timing, and duration of skin-to-skin contact between the mother and infant

#### Baseline characteristics for both studies include:

•Gestational age•Biological sex at birth•Birth weight

### Maternal outcomes

Maternal outcomes will also be assessed, including estimated total blood loss, placental weight, and surgical site infection after caesarean section.

### Sample size

Patient enrolment will span 4 years, aiming to include 25 newborns in study phase 1 and 100 newborns across all centres in study phase 2. The sample size estimation is based on feasibility considerations and expected birth rates at the participating centres over the 4-year study period. As this is a prospective, descriptive, observational study design, no formal sample size calculation was performed.

### Adverse event reporting

Infants with CHD, such as TGA, are inherently at high risk for serious complications.^3^ Previous studies have shown PBCC to be feasible and safe in preterm and term infants.^13^, ^14^, ^15^, ^16^ All serious adverse events directly related to the stabilisation approach will be systematically recorded in case report forms and evaluated in both studies and presented to ensure comprehensive safety monitoring. Any unexpected or unusual serious adverse events observed during the single-centre feasibility study will be reviewed, and the protocol may be modified or the study terminated if deemed necessary before implementing the protocol in multiple European centres.

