### Statistical analysis

Feasibility will be assessed by the proportion of successful stabilisation (without protocol deviations), protocol adherence, and stabilisation-related adverse events, whereas safety will be evaluated based on the occurrence and incidence of serious adverse events. Descriptive clinical outcomes in study phase 2 include the incidence and severity of PPHN; the frequency, timing, and escalation of invasive respiratory and circulatory interventions; and the occurrence of adverse events directly related to the stabilisation approach. Outcomes will be summarised using descriptive statistics and compared with existing literature. Categorical variables will be reported as frequencies and percentages, and continuous variables will be reported as means ± standard deviations or medians with interquartile ranges, depending on distribution. Within the study cohort, comparative analyses between subgroups (eg, TGA with intact ventricular septum vs TGA with ventricular septal defect and infants with vs without PPHN) will be conducted using χ^2^ or Fisher exact tests for categorical variables and independent samples *t* tests or Mann-Whitney *U* tests for continuous variables, as appropriate. Missing data will be handled appropriately and reported. A *P* value of <0.05 will be considered statistically significant. As this is an observational cohort study, no multiplicity adjustments, stopping guidelines, or formal interim analyses for early termination are planned.

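### SAE recording is restricted to events attributed to the stabilisation approach, yet safety is to be judged on SAE incidence without that restriction

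*Protocol article*

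**What the plan says.** The recording rule is in Adverse event reporting: "All serious adverse events directly related to the stabilisation approach will be systematically recorded in case report forms". It covers both studies. The next sentence adds a review for phase 1 that does not depend on cause: "Any unexpected or unusual serious adverse events observed during the single-centre feasibility study will be reviewed".

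Under Primary outcome, phase 1 safety is described as follows: "Safety assessments are based on any unintended events directly related to the bedside stabilisation and neonatal parameters". The neonatal parameters (temperature, haemoglobin and polycythaemia, bilirubin and its treatment) and maternal blood loss carry no causality condition. The phase 1 outcome also includes "the number of adverse events in the delivery room", again without one.

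Statistical analysis states that "safety will be evaluated based on the occurrence and incidence of serious adverse events". For phase 2 it lists, among the descriptive outcomes, "the occurrence of adverse events directly related to the stabilisation approach".

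**The concern.** Two stated rules do not fit together. One decides what enters the case report form and filters on cause. The other names the safety measure and does not filter. Anyone following the first arrives at the analysis with a subset of the events that the second needs.

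The filter matters more here than in a controlled trial. There is no concurrent group in which the same attribution errors would occur, so the count is not protected by a comparison. Adverse event reporting itself notes that infants with congenital heart disease carry a high inherent risk of serious complications. An SAE in such an infant can plausibly be put down to the heart defect, and nothing within the cohort can test that judgement. The resulting count can only be equal to or lower than the all-cause count. If it is then compared with published all-cause rates, the approach will look safer than it is.

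Safety is part of the phase 1 primary outcome, and phase 1 is meant to inform whether and how the protocol goes to other European centres.

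**Working it through.** The article gives no SAE rate, and its Sample size section says that no formal calculation was made. There is no figure of the plan's own to reproduce, so the main check is to set the sections side by side.

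**1. Do the two rules conflict, or is one shorthand for the other?** The Statistical analysis sentence that defines safety also defines feasibility. In its feasibility half it limits adverse events to those related to stabilisation. In its safety half it names SAEs with no such limit. With the qualifier present in one half and absent from the other, the plain reading is that safety means all SAEs. Adverse event reporting does not promise to record all SAEs.

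**2. What is collected regardless of cause?**
- Both phases, Secondary outcome: preoperative survival, non-invasive and invasive respiratory interventions, iNO, balloon atrial septostomy, ECMO.
- Both phases, Primary outcome and the additional phase 2 outcomes: temperature at ICU admission, haemoglobin and polycythaemia, bilirubin, phototherapy or exchange transfusion.
- Maternal outcomes: blood loss, placental weight, surgical site infection after caesarean section.
- Phase 1 only: delivery-room adverse events, and review of unexpected or unusual SAEs.

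**3. What is left?** An SAE that is judged unrelated and is not a listed outcome. In phase 1 it must also fall outside the delivery room and be neither unexpected nor unusual. A neurological event is an example, since none is listed in the outcome sections. For phase 2 no review of unexpected or unusual SAEs is stated, and the phase 2 adverse event outcome is itself limited to related events, so the gap is widest there.

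**4. How much could a filter hide? (illustration only)** Inputs: n = 25 for phase 1 and n = 100 for phase 2, from Sample size. Assumptions, not in the document: each infant independently has an SAE with probability p, and a share s of these is judged related and so recorded. Then the expected recorded incidence is p × s, and P(none recorded) = (1 − p·s)^n.

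For n = 25:

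| True risk p | All recorded (s = 1) | Half judged related (s = 0.5) | A quarter judged related (s = 0.25) |
|---|---|---|---|
| 5% | 0.95^25 = 27.7% | 0.975^25 = 53.1% | 0.9875^25 = 73.0% |
| 10% | 0.90^25 = 7.2% | 0.95^25 = 27.7% | 0.975^25 = 53.1% |
| 20% | 0.80^25 = 0.4% | 0.90^25 = 7.2% | 0.95^25 = 27.7% |

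For n = 100 and p = 10%, the three values are below 0.1%, 0.6% and 8.0%. In expectation, 10 events among 100 infants become 5 with s = 0.5.

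**5. What would a count of zero mean?** The exact two-sided 95% upper limit is 1 − 0.025^(1/n), which is 13.7% for n = 25 and 3.6% for n = 100. Under the filter these limits bound only the rate of SAEs judged related. They say nothing about the all-cause rate that Statistical analysis names.

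**The case against.** The best defence is that the Statistical analysis wording is shorthand for the SAEs that Adverse event reporting has already defined, and that SAE definitions, windows and relatedness assessment commonly sit in a full protocol that is not shown. The second part stands: who judges relatedness, and by what criteria, is not counted as a gap. The first part is possible but strained, for the reason in step 1 of the working. Two stated rules that differ are also not the same as missing detail.

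The other strong argument is the amount collected without any filter. It defeats several stronger readings that a reader might infer:

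- *That other SAEs are never captured, including deaths and ECMO runs attributed to the heart defect.* Not supported. Preoperative survival is a secondary outcome in both phases, as are "administration of iNO administration, balloon atrial septostomy, and extracorporeal membrane oxygenation".
- *That a conclusion of safety would rest on the causality filter alone.* Not supported. Phase 1 safety also uses the unfiltered neonatal and maternal parameters and the delivery-room count.
- *That SAE incidence is the only quantity comparable with outside data.* Not supported. Survival and the listed interventions can be compared as well.
- *That Statistical analysis drops temperature, polycythaemia, bilirubin and blood loss from safety.* Not supported. They are named under Primary outcome, and Statistical analysis says that outcomes will be summarised descriptively.
- *That missed events are lost for good.* Too strong. Source documents are archived for at least 15 years, so events could be sought by chart review, though not as systematically as by prospective recording.

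It is also fair to say that the probabilities above rest on assumed inputs, that no rule in the article turns zero SAEs into a declaration of safety, and that the Limitations section claims only a preliminary evaluation.

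**Conclusion.** The point holds in a bounded form. The recording rule yields only SAEs attributed to the approach, the analysis section promises SAE incidence without that limit, and the first cannot supply the second. In an uncontrolled cohort with high background risk, the filtered count is biased towards safe and is not comparable with all-cause rates in the literature. The events affected are SAEs judged unrelated and not among the listed outcomes, with the widest gap in phase 2.

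The size cannot be taken from the document. Under the assumptions stated in the working, with half of SAEs judged related, the recorded incidence is half the true one. The chance of recording none among 25 infants then rises from 27.7% to 53.1% at a 5% risk, from 7.2% to 27.7% at 10%, and from 0.4% to 7.2% at 20%. These figures describe the SAE record only. An event that is also a listed outcome would still be seen elsewhere in the data.

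**What to change.** In Adverse event reporting, record every SAE in both phases over a defined window, for example from birth to the arterial switch operation, discharge or death, with relatedness as a separate field. In Statistical analysis, report all-cause SAE incidence with an exact 95% confidence interval and show related SAEs as a subset.

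If this is not done, Statistical analysis must say that the safety measure is SAEs judged related only, and that it is not comparable with all-cause rates in the literature.

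The cost is a change to protocol and case report form wording and some extra entries per infant, for events that are already in the clinical record.

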### Statistical analysis

Feasibility will be assessed by the proportion of successful stabilisation (without protocol deviations), protocol adherence, and stabilisation-related adverse events, whereas safety will be evaluated based on the occurrence and incidence of serious adverse events. Descriptive clinical outcomes in study phase 2 include the incidence and severity of PPHN; the frequency, timing, and escalation of invasive respiratory and circulatory interventions; and the occurrence of adverse events directly related to the stabilisation approach. Outcomes will be summarised using descriptive statistics and compared with existing literature. Categorical variables will be reported as frequencies and percentages, and continuous variables will be reported as means ± standard deviations or medians with interquartile ranges, depending on distribution. Within the study cohort, comparative analyses between subgroups (eg, TGA with intact ventricular septum vs TGA with ventricular septal defect and infants with vs without PPHN) will be conducted using χ^2^ or Fisher exact tests for categorical variables and independent samples *t* tests or Mann-Whitney *U* tests for continuous variables, as appropriate. Missing data will be handled appropriately and reported. A *P* value of <0.05 will be considered statistically significant. As this is an observational cohort study, no multiplicity adjustments, stopping guidelines, or formal interim analyses for early termination are planned.

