## Abstract

At birth, major circulatory and pulmonary adaptations are required for a successful foetal-to-neonatal transition. In newborns with transposition of the great arteries (TGA), this transition is often impaired, leading to severe hypoxemia. This may also result in persistent pulmonary hypertension of the newborn (PPHN), worsening hypoxemia, and increasing the risk of urgent invasive interventions after birth. Physiological-based cord clamping (PBCC), delaying cord clamping until after lung aeration and ventilation are established, promotes a more stable circulatory transition and has shown benefits in both preterm and term neonates. PBCC may also provide advantages in infants with congenital heart disease. In TGA, combining PBCC with early supplemental oxygen may reduce the incidence and severity of PPHN, decrease related complications, and minimize the need for invasive interventions. To evaluate the feasibility, safety, and clinical outcomes of the stabilisation approach, we have initiated a stepwise quality improvement initiative comprising 2 sequential studies. Study phase 1, a single-centre study at Leiden University Medical Centre will assess feasibility, protocol adherence, and safety. Study phase 2, an observational cohort study across multiple European centres will evaluate clinical outcomes, focusing on incidence and severity of PPHN and the need for urgent interventions. All TGA newborns will be stabilised with an intact umbilical cord while receiving 2 L/min nasal high flow (fraction of inspired oxygen 1.0) as supplemental oxygen. Cord clamping will occur once the infant is considered stable, defined as a heart rate >100 bpm and preductal SpO_2_ >75% with supplemental oxygen. This study will inform guidelines for delivery room management and early preoperative care in TGA newborns.

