### Hypothesis

We hypothesise that a stabilisation approach combining PBCC with early supplemental oxygen is both feasible and safe, and will enhance transitional circulation in newborns with TGA. This approach is expected to reduce the incidence and severity of PPHN, minimise PPHN-related complications, decrease the need for urgent invasive interventions, and shorten intensive care unit (ICU) stay.

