### Study population

The study includes all prenatally diagnosed newborns with TGA (with or without ventricular septal defect) delivered at participating centres. Infants with complex TGA (ie, TGA with aortic coarctation, left ventricular outflow tract obstruction, or Taussig-Bing anomaly) are excluded.

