### Limitations

This study focuses on newborns with TGA, which may limit the generalisability of the results to the broader CHD population. The target sample size is 25 infants for study phase 1 and 100 infants across all centres for study phase 2. This sample size was determined based on feasibility considerations rather than a formal power calculation. Although this design allows for a preliminary evaluation of the clinical outcomes of the stabilisation approach, multicentre studies with larger sample sizes will be required to draw definitive conclusions regarding its effectiveness.

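### The reduction part of the aim and hypothesis has no comparator in the design, and a larger single-arm cohort would not supply one

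*Protocol article*

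**What the plan says.** The Hypothesis section has two parts. One is that the approach "is both feasible and safe, and will enhance transitional circulation in newborns with TGA". The other is comparative: "This approach is expected to reduce the incidence and severity of PPHN, minimise PPHN-related complications, decrease the need for urgent invasive interventions", and also "shorten intensive care unit (ICU) stay". The section on the aim of the study likewise makes reduction of PPHN and of early invasive interventions the overall aim.

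No control group appears in the design. The Abstract states "All TGA newborns will be stabilised with an intact umbilical cord", and the introduction calls a randomised trial infeasible without putting a historical or concurrent cohort in its place. Under Statistical analysis, "Outcomes will be summarised using descriptive statistics and compared with existing literature". The only tests described there are between subgroups of the treated cohort.

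On who is studied, the Study population section says "The study includes all prenatally diagnosed newborns with TGA", with or without VSD, and excludes complex TGA. On the outcome, Study procedures classifies PPHN for this study by iNO given for more than 12 hours. The phase 2 primary outcome assesses PPHN by pre- and postductal saturation difference, echocardiography and escalation of interventions.

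The Limitations section explains the restricted conclusions by the sample size, which was set by feasibility, and adds that "multicentre studies with larger sample sizes will be required to draw definitive conclusions regarding its effectiveness".

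**The concern.** Less PPHN, fewer interventions and a shorter stay are statements about a difference, and a difference needs a second quantity. The design supplies none. The literature comparison fixes no source, reference rate, outcome definition or adjustment.

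Three features of the study make a published rate hard to carry over. The PPHN rule depends on a treatment decision and is declared specific to this study. The cohort is restricted to prenatally diagnosed, non-complex infants born at tertiary centres. It also mixes two anatomical groups, although the introduction says impaired transition concerns intact-septum infants in particular.

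If phase 2 shows a lower percentage than some published series, readers may take it as benefit, and the Conclusions section says the findings will inform guidelines. The Limitations section would point them to the wrong remedy: more infants rather than a comparator.

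**Working it through.** **No figure to reproduce.** The article gives targets of 25 infants (phase 1) and 100 (phase 2), set by feasibility. It states no reference PPHN rate, effect size or power. All rates below are assumptions chosen to show scale.

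**Step 1: the parts of the hypothesis against the design.**
- Feasible and safe: phase 1 primary outcome; one arm suffices.
- Description of clinical outcomes: phase 2 focus; one arm suffices.
- Less PPHN and fewer interventions: outcomes are collected, but there is no control, only the literature.
- Shorter ICU stay: no control, and ICU stay is in none of the article's outcome lists.

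**Step 2: case mix alone.** Overall rate = s × p(IVS) + (1 − s) × p(VSD), where s is the intact-septum share. There is no treatment effect in any row.

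| Assumed p(IVS) / p(VSD) | s = 50% | s = 80% | Gap (points) |
|---|---|---|---|
| 25% / 8% | 0.5×25 + 0.5×8 = 16.5% | 0.8×25 + 0.2×8 = 21.6% | 5.1 |
| 25% / 5% | 15.0% | 21.0% | 6.0 |
| 30% / 10% | 20.0% | 26.0% | 6.0 |
| 20% / 10% | 15.0% | 18.0% | 3.0 |

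**Step 3: sampling error for comparison.** At n = 100, an observed 20/100 has a Clopper-Pearson 95% interval of 12.7% to 29.2%. At this size, imprecision exceeds the case-mix gap.

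**Step 4: does a larger sample help?** The protocol plans no test against an external rate, so this is only an illustration. Take a true rate of 16.5% (50% intact septum) and a fixed literature rate of 21.6% (80% intact septum). Use an exact binomial lower-tail test at one-sided 0.025. The critical count c is the largest count with P(X ≤ c | n, 0.216) ≤ 0.025. The chance of a false reduction is P(X ≤ c | n, 0.165).

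| n | c | False reduction |
|---|---|---|
| 100 | 13 | 21% |
| 400 | 70 | 73% |
| 1000 | 190 | 98% |

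The bias stays the same size while the interval narrows, so the false finding becomes more likely as the cohort grows.

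**Step 5: a general shift.** Suppose definition or case mix alone makes the background rate 25% lower, in relative terms, than the literature rate. At n = 100 the same test finds a false reduction in 12%, 16% or 32% of studies at literature rates of 10%, 20% or 30%.

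**Step 6: what a control cohort would give.** Consider 100 treated against 100 controls, two-sided 0.05, with PPHN halved. Power = Φ{[d − 1.96√(2p̄(1−p̄)/n)] / √([p₁(1−p₁) + p₂(1−p₂)]/n)}, where d = p₁ − p₂ and p̄ is the mean of the two rates. For 20% against 10%: (0.10 − 1.96 × 0.0505) / 0.05 ≈ 0.02, so power is about 51%. At control rates of 10% and 30%, power is about 27% and 72%. For 80% power, 435, 199 or 121 infants per group are needed at control rates of 10%, 20% or 30%.

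**The case against.** The article calls the design descriptive in several places and presents phase 2 as evaluation and description. It describes the evaluation as preliminary and disclaims definitive conclusions on effectiveness. Much of its language on benefit is hedged. It plans no formal test against an external rate. The intact-septum versus VSD comparison is the first subgroup analysis it names, so septal status has not been overlooked. At 100 infants, sampling error is larger than the illustrated case-mix gap, so naming sample size as a limit is incomplete rather than wrong.

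All of this stands, and it narrows the point. It does not remove it: a descriptive design and a reduction hypothesis sit in the same document, and the stated limitation omits the reason they do not fit together.

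A reader might infer more than the documents support:
- **That the study cannot answer its own question.** Feasibility, safety and description can all be addressed in one arm.
- **That the literature is mismatched or will be chosen after the data are seen.** No series is named and no time of selection is given, so comparability is unspecified rather than shown to be absent. A fuller document may name the series.
- **That the iNO rule shifts the incidence by a known amount.** The documents give nothing from which to derive one.
- **That only a pooled PPHN rate will be reported.** The article does not say so.

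**Conclusion.** The point holds for the reduction part of the aim and hypothesis. This is a stated design choice and not a detail left to a fuller document: an analysis plan could name published series, but it could not create a control that the design lacks. A lower PPHN rate than in the literature could not be attributed to the approach, whatever the sample size.

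On the assumed rates, a change in intact-septum share from 50% to 80% produces a gap of 3 to 6 points with no treatment effect. The actual size is unknown, because the article gives neither stratum rates nor a reference rate. The conclusion does not depend on the particular figures. It needs only that PPHN risk differs by septal status, as the introduction implies, or that published series differ from this cohort in definition, case mix or era.

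**What to change.** 1. **Restate the aim, hypothesis and conclusions.** Phase 2 estimates PPHN incidence and intervention rates under the new approach, with confidence intervals. Say that the literature comparison gives context and supports no claim of reduction.
2. **Correct the Limitations section.** Name the absence of a concurrent or matched control as the main limit on effectiveness conclusions, alongside sample size.
3. **Build on the planned septal-status split.** Report PPHN separately for intact-septum and VSD infants. Make any literature comparison within those strata, and only with series that use a comparable PPHN definition.

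These changes cost wording and tabulation; the downside is a less favourable claim.

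If a comparison is wanted, a pre-adoption cohort from the same centres, with the same eligibility and outcome definitions, is an option and not a requirement. It needs record extraction at each centre, keeps confounding by era, and has limited power at 100 per group (about 27% to 72% for a halving, on the assumed control rates).

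### Subgroup comparisons in a descriptive, feasibility-sized cohort are judged at P < 0.05; a difference with a 95% confidence interval would serve better (minor)

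*Protocol article*

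**What the plan says.** The Statistical analysis section of the protocol article plans comparisons within the cohort and gives two examples: "TGA with intact ventricular septum vs TGA with ventricular septal defect and infants with vs without PPHN". Categorical variables are compared by chi-squared tests or "Fisher exact tests for categorical variables", and continuous variables by independent-samples t or Mann-Whitney "tests for continuous variables, as appropriate". The decision rule is a P "value of <0.05 will be considered statistically significant", and the section says that no multiplicity adjustment is planned.

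The stated summaries are by group: "Categorical variables will be reported as frequencies and percentages", and means with standard deviations or medians with interquartile ranges for continuous variables. The article names no estimate of a between-group difference and no confidence interval.

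The Sample size section aims for 25 newborns in phase 1 and 100 in phase 2. It bases these numbers on feasibility and expected births, calls the study descriptive, and says that there was no formal calculation. The Limitations section calls the evaluation preliminary and leaves definitive conclusions on effectiveness to larger studies.

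**The concern.** A study that describes its outcomes without a power calculation has little use for a significant/not-significant verdict on its subgroups. Unless power is high, a non-significant P value does not separate groups that behave alike from groups that differ by a clinically important amount. What separates the two is the interval around the difference, and the stated output does not include it.

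At stake is how the comparison of anatomical groups, and of infants with and without PPHN, will be read. A reader who sees two percentages and a P value above 0.05 may take the groups to be similar when the data are compatible with a large difference. The phase 2 summaries for the whole cohort do not depend on these tests.

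**Working it through.** **Inputs from the article.** Phase 2 has 100 infants (Sample size). The threshold is 0.05 (Statistical analysis), taken here as two-sided because the article does not say. It states no power, so there is no figure of its own to reproduce.

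**Assumptions.** The article gives neither the anatomical split nor PPHN rates by anatomy. The main illustration takes 65 infants with intact septum and 35 with VSD. Other splits are shown as a range.

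**1. Power of the Fisher test.** Power is the sum, over all pairs of event counts (x1, x2) with Fisher P < 0.05, of Bin(x1; n1, p1) × Bin(x2; n2, p2), by exact enumeration.

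| PPHN rates | 65/35 split | 75/25 split |
|---|---|---|
| 15% vs 5% | 0.240 | 0.144 |
| 20% vs 8% | 0.307 | 0.203 |
| 30% vs 10% | 0.635 | 0.495 |

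| PPHN rates | 50/50 split | 60/40 split | 70/30 split |
|---|---|---|---|
| 20% vs 10% | 0.195 | 0.223 | 0.158 |
| 30% vs 10% | 0.640 | 0.651 | 0.537 |

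For moderate differences the usual result is non-significance. For 30% versus 10% significance is the more likely result, except at 75/25, where it is about an even chance.

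**2. What the P value leaves out.** Suppose PPHN is seen in 13/65 (20.0%) and 3/35 (8.6%). The difference is 0.2000 - 0.0857 = 0.1143, and Fisher P = 0.16.

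The Newcombe interval combines the Wilson limits of each proportion:

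- 13/65: 0.1208 to 0.3127
- 3/35: 0.0296 to 0.2238
- Lower limit = 0.1143 - √[(0.2000 - 0.1208)² + (0.2238 - 0.0857)²] = 0.1143 - 0.1592 = -0.045
- Upper limit = 0.1143 + √[(0.3127 - 0.2000)² + (0.0857 - 0.0296)²] = 0.1143 + 0.1259 = +0.240

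So P = 0.16 goes with an interval from -4.5 to +24 percentage points.

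**3. The same at a 60/40 split.**

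- 12/60 versus 4/40: difference 10 points, 95% CI -5 to +23, Fisher P = 0.27.
- 12/60 versus 8/40: difference 0, 95% CI -17 to +15, Fisher P = 1.0.

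Even equal observed rates leave differences of about 15 points in either direction open.

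**4. Continuous outcomes.** At 65/35 the standard error of a mean difference is √(1/65 + 1/35) = 0.21 SD, so the 95% half-width is about 1.96 × 0.21 = 0.41 SD. A difference of about 0.57 to 0.62 SD is needed for 80% power across splits from 50/50 to 70/30.

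**The case against.** **This is left to the analysis plan.** Only a condensed article is at hand, and intervals may well be specified in a statistical analysis plan. That is fair as regards anything the article merely omits. But the article does state the tests and the threshold for these comparisons, and that rule can be judged as written.

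**The difference can be read off.** If percentages, or means with standard deviations, are shown by subgroup, a reader can subtract them and work out an approximate interval. This stands for the point difference, so the tests are not reported bare. The reader should not have to derive the precision, and medians with interquartile ranges do not yield an interval for the contrast.

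**The limits are disclosed.** A reader might infer that a null result will be presented as no difference. The article does not say so, and the Sample size and Limitations sections partly guard against it. The Conclusions' sentence on informing guidelines concerns the stabilisation approach, not the equivalence of anatomical groups. Only the weaker statement holds: a non-significant result may be misread. Low power in a cohort openly sized on feasibility is likewise no error in itself.

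**Should the comparisons be adjusted?** Gestational age and birth weight are listed under "Baseline characteristics for both studies include", so a reader might infer that they ought to enter the comparisons, and that any imbalance would pass as a subgroup effect. The article does not support that reading. It gives these contrasts no causal aim, and an unadjusted difference is a legitimate descriptive target. Septal anatomy precedes gestational age at delivery and birth weight, so adjusting could condition on its consequences. When infants with and without PPHN are compared, these variables may be among those compared. The article also gives no data on imbalance or prognostic strength.

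**Conclusion.** The point holds as a minor improvement. The stated rule gives a significance verdict where a descriptive, preliminary cohort calls for an estimate with its precision. Under an assumed 65/35 split of 100 infants, power is about 24% to 31% for moderate PPHN differences and 64% for 30% versus 10%. A non-significant result can accompany an interval reaching +24 points.

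These figures rest on assumed splits and event rates. The 24% to 31% range falls to 14% to 20% at 75/25. The case for an interval does not depend on any one scenario.

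The documents do not establish that the sponsor will misread a null result, or that covariate adjustment is needed.

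**What to change.** In the Statistical analysis section, replace the P < 0.05 verdict for subgroup contrasts with the estimated difference and its 95% confidence interval:

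- **Binary outcomes:** risk difference with a Newcombe interval.
- **Continuous outcomes:** mean difference with its interval, or the Hodges-Lehmann shift with its interval where Mann-Whitney is used.
- **Wording:** label these comparisons as exploratory, unadjusted associations, and state that non-significance is not evidence of no difference.

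No covariate adjustment is proposed.

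The cost is a few lines of text and code, and a little more analysis and reporting. No new data are needed and the design does not change. The one downside is that the intervals will be wide and look less decisive than a verdict.
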